
#### Baseline Assessment

Information concerning stroke diagnosis, medical history and stroke onset will be acquired from patient records, from which participant characteristics will also be collected: sex, age, medication use, co-morbidities, side and location of the lesion, days post-stroke, stroke severity as assessed by NIHSS and modified Rankin Scale (mRS) and immediate treatment for stroke (thrombolysis/thrombectomy).

### 2.8. Statistical Analysis

The main analysis population will be defined by intention-to-treat, comprising all randomised participants with a baseline assessment, regardless of later events such as protocol violations, missing data or loss to follow-up. Missing data will be imputed and the impacts of imputation on results will be explored. Secondary analyses will be conducted, restricted to the population of participants who followed the study protocol and had no missing data.

General linear models with repeated measures design will be used to test the effect of the Core Stability program (with or without TENS) on the change in the outcome of interest (total S-TIS 2.0 score or any other outcome) between the baseline and follow up (five weeks), using a repeated measures design with two levels (baseline, five weeks), as well as a two-level factor testing the intervention (usual care). The models will adjust for clinically relevant covariates, such as site, age, baseline levels of the dependent outcomes or severity of stroke. Similar models will be built to explore the effect of Core Stability at different time points (three months; six months). Similar models will test the effect of TENS added to Core Stability on primary and secondary outcomes, as well as primary and secondary endpoints.

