## 2. Materials and Methods

### 2.1. Study Design and Setting

This study is an assessor-blinded, multicenter RCT, with a five-week treatment period followed by a three-to-six-month follow-up. It follows the consensus-based core recommendations from the stroke recovery and rehabilitation expert group [42] and the SPIRIT statement [43]. Participants will be randomly allocated (at a ratio of 2:1:1) to the control group (CG) (*n* = 110) or the experimental group (EG with and without TENS) (*n* = 110), <15 and >15 days after stroke. Patients are being recruited by inpatient rehabilitation hospitals in six centers in Catalonia: Hospital Universitari Parc Taulí de Sabadell; Hospital-Consorci Sanitari de Terrassa; Fundació Hospital de la Santa Creu de Vic; Hospital Sagrat Cor Germanes Hospitalaries de Martorell; Hospital Sociosanitari Mutuam Girona; and Centre Fòrum Parc de Salut Barcelona.

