All data are recorded on-line using an electronic data form Clinapsis^®^, available from the study coordinating center. All investigators were trained in the use of the application and have a help guide, as well as a consultation service directly with the logistics coordinator of the study. Access to the study database is restricted to authorised study personnel by password.

For the calculation of the sample size, we have assumed that conventional rehabilitation will be associated with a clinically relevant change in the Trunk Impairment Scale at five weeks compared to the baseline. The minimal clinically relevant difference has been established as 3-point [44]. We have also assumed that rehabilitation by CSEs program will add a benefit of 1.6 points at five weeks, equivalent to 10% in the scale. That is, the experimental group with CSE will present a change of 4.6 points at five weeks with respect to the baseline situation (intragroup). Assuming a common standard deviation of 4 [45], and estimating a 10% lost at follow-up, accepting an alpha risk of 0.05 and a beta risk of less than 0.2 in a bilateral contrast, it will be necessary to include 110 patients in each group to detect a difference between groups of 1.6 points or higher on the total S-TIS 2.0 scale. The calculation of the sample size was done with the GRANMO program.

If a patient, either in CG or EG, has to withdraw from the treatment sessions due to a transient disease or mind trauma, he or she may be re-included if the dropout period is shorter than 10 days. Patients are allowed to withdraw from the study for any reason, and no adverse events have been described previously.

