### 2.6. Participant Timeline

The study has five assessments: T0 (baseline), T1 (week three, only primary outcomes), T2 (week five, end-point, 25 sessions), T3 (week 17) and T4 (week 29). Study duration per patient: 29 weeks (See Figure 2).

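### The primary model uses baseline as both response and covariate and does not say which term is the treatment effect, so some fits the wording allows report half the effect or understate its standard error

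*Protocol article*

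**What the plan says.** Section 2.8 sets out the main model in two sentences. The first says that general linear models with repeated measures will test the programme's effect on the change in the outcome from baseline to five weeks, "using a repeated measures design with two levels (baseline, five weeks), as well as a two-level factor testing the intervention (usual care"). Baseline is therefore one of the two response levels, and the only intervention term named is a two-level factor. The second reads: "The models will adjust for clinically relevant covariates, such as site, age, baseline levels of the dependent outcomes or severity of stroke". The baseline value of the same outcome is thus offered as a covariate as well.

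Similar models are announced for three months, six months and the TENS comparison, so the wording carries over to them.

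Section 2.2 gives the target: "rehabilitation by CSEs program will add a benefit of 1.6 points at five weeks". Section 2.6 adds an interim visit, "T1 (week three, only primary outcomes"), for which section 2.8 names no analysis.

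**The concern.** With responses at baseline and five weeks, the model has two candidate treatment terms. The group factor averages the arm difference over both visits. Randomisation makes the expected difference at baseline zero, so this term estimates half the five-week effect. The group-by-time term estimates the whole of it. The sentence names the first and implies the second.

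Using baseline again as a covariate adds a second ambiguity. Baseline predicts itself with slope 1 and the five-week score with a smaller slope. A fit that forces one common slope on both visits therefore gets the residual variance wrong.

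At stake is the headline result of a trial powered on 1.6 points: its reported size, its power and its error rate could depend on a software default.

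**Working it through.** **Inputs.** From section 2.2: difference 1.6; "Assuming a common standard deviation of 4 [45], and estimating a 10% lost at follow-up"; a two-sided test at 5% with power of at least 80%. From section 2.1: allocation "randomly allocated (at a ratio of 2:1:1) to the control group (CG"), which is 1:1 for control against the pooled experimental group. Assumptions: pre-post correlation r = 0.3, 0.5 or 0.7, and SD 4 read as the SD of the score at each visit.

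**The plan's own figure.** n = 2 × 4² × (1.96 + 0.8416)² / 1.6² = 98.1, so 99 per group; 99 / 0.9 = 110. This matches "it will be necessary to include 110 patients in each group". The sample size is not in question. The rest uses n = 99 evaluable per group, s = 4 and a true five-week effect of 1.6. Power is Φ(estimate/SE − 1.96).

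**1. ANCOVA of the five-week score on arm and baseline.** Estimate 1.6; SE² = 2s²(1 − r²)/n.

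**2. Classical repeated-measures fit, baseline crossed with time, group-by-time term.** This regresses (Y − B) on arm and B, where B is the baseline score and Y the five-week score. Subtracting B changes only the slope on B, so the arm coefficient, SE and p-value are those of ANCOVA.

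**3. Same fit, group factor.** This regresses (B + Y)/2 on arm and B. The coefficient is 0.8 and its SE is also halved, so the p-value equals ANCOVA's while the reported effect is half.

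**4. Group factor, baseline not a covariate.** Estimate 0.8; SE² = s²(1 + r)/n.

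**5. Group-by-time term, baseline not a covariate (change score).** Estimate 1.6; SE² = 4s²(1 − r)/n.

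**6. Stacked fit, one common baseline slope, group-by-time term.** The estimate is still the raw change difference, so its true SE is that of fit 5. The common slope is (1 + r)/2, the average of 1 and r. The residual variances are s²(1 − r)²/4 at baseline and s²(1 − r²) + s²(1 − r)²/4 at five weeks. Pooling them gives model SE² = s²(1 − r)(3 + r)/n, so model SE / true SE = √((3 + r)/4). Type I error is 2[1 − Φ(1.96 × ratio)].

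| | r = 0.3 | r = 0.5 | r = 0.7 |
|---|---|---|---|
| Fits 1 and 2: SE | 0.542 | 0.492 | 0.406 |
| Fits 1 and 2: power (also fit 3, estimate 0.8) | 84% | 90% | 98% |
| Fit 4: SE (estimate 0.8) | 0.458 | 0.492 | 0.524 |
| Fit 4: power | 42% | 37% | 33% |
| Fit 5: SE | 0.673 | 0.569 | 0.440 |
| Fit 5: power | 66% | 80% | 95% |
| Fit 6: model SE | 0.611 | 0.532 | 0.424 |
| Fit 6: type I error | 7.5% | 6.7% | 5.9% |

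Simulation agrees. Power was 82/89/97% for ANCOVA and 65/79/95% for the change score. Type I error for fit 6 was 7.7/6.7/6.1% in 20,000 null trials per correlation. A random-intercept fit, checked in only 30 runs at r = 0.3, showed the same pattern as fit 6 (intercept variance near zero, model SE 0.60 against an empirical 0.75).

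**Sensitivity: narrower baseline.** Entry requires S-TIS 2.0 of at most 10 (section 2.4), so the baseline SD may be below 4. Take baseline SD 3, β = 4r/3 and D = 9(1 − β)². The squared SE ratio in fit 6 becomes [32(1 − r²) + D] / [32(1 − r²) + 2D]. Type I error falls to 6.2/5.5/5.0%. The halved estimate in fits 3 and 4 does not change.

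**Sensitivity: SD 4 is the SD of change.** The change score then has 80% power at every r, ANCOVA 94/90/86%, and fit 4 54/37/22%.

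**The case against.** The best defence is that the sentence states its target, an effect on change from baseline to five weeks, and in this layout that is the group-by-time contrast. The model class named is a general linear model with repeated measures, where covariates are normally crossed with time. Read that way, the plan is fit 2 and is sound. The article mentions no random intercept, and the covariate list is illustrative, so the double use of baseline is likely but not fixed.

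Most of this stands, and it rules out three stronger readings:

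- A reader might infer that the model must either halve the effect or misstate its standard error. It need not: fit 2 does neither.
- A reader might infer that power could fall to about 36% under the plan as worded. That needs the group factor to be the test and baseline to be left out as a covariate. With baseline in a classical fit, the p-value is ANCOVA's.
- A reader might infer that the week-three data are never used. The article names no analysis of them, but a condensed article cannot show that. A fuller analysis plan or the imputation announced in section 2.8 may use them.

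The defence does not settle which coefficient will be reported. The only intervention term named is the two-level factor, and baseline is written on both sides of the model.

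**Conclusion.** The point holds in limited form. Section 2.8 lists baseline as a response level and as an example covariate, and does not name the contrast that carries the treatment effect. A sound fit is available within the wording, but so are fits that report 0.8 for a true 1.6, or that test the interaction at about 6% to 8% in place of 5%. If baseline is dropped, the change score loses power against ANCOVA: 66/80/95% against 84/90/98% if SD 4 is the SD of the score.

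The halving follows from randomisation alone. The error rates and power depend on the assumed correlations and on how SD 4 is read, and the type I inflation shrinks if the entry limit narrows the baseline spread. This should be fixed before the analysis, but it is not a fatal defect. The missing week-three analysis is not counted as an error.

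**What to change.** In section 2.8, state that the primary estimate is the arm contrast at five weeks (T2) from an ANCOVA of the T2 score on arm, baseline score and a closed list of prespecified covariates. Alternatively, take the same T2 contrast from a mixed model whose responses are post-baseline visits only, with arm-by-visit and baseline-by-visit terms and unstructured within-patient covariance. In either case baseline enters once, as a covariate, and is not also a response. Apply the same form to the three-month, six-month and TENS models.

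Using the week-three primary-outcome data in the mixed model or the imputation is an optional gain. The cost is a change of wording, with no new data or patients.

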## 3. Discussion

Motor rehabilitation after stroke continues to be an area in need of substantial financial and scientific investment. There is also a need for more pragmatic trials to test interventions in a way that assists their translation into clinical practice. The analysis of recovery in subacute phase profiles is important, as this information can provide a more specific plan for stroke rehabilitation in this phase. Exercise intensity and type is not only the most challenging parameter to determine, but it is also the most critical one to ensure that a dose is safe, attainable and adequate to elicit a training effect. A previous study demonstrated that the repetitive movement may be the best to stimulate cerebral neural plasticity [65]. CSEs are repetitive movements in different positions. CSEs in this study are not only performed in the supine position – when possible, they are performed in the sitting position. Training of vertical trunk function is important because humans stand and move using two legs [66].

We hope that dynamic sitting balance and gait will be better in EG than CG. Concerning gait, a minimal detectable change of 1 point for BBA (stepping) would be a good result [67]. Regarding standing balance, a difference change of ± 6 points for BBS is necessary to be 90% confident about a genuine change during inpatient stroke rehabilitation [68,69]. It has been reported more recently that a change of 4.8 points in the FIST is clinically important [70]. 

The co-activation of the diaphragm, transversus abdominis and internal oblique improves postural control [71] – these muscles are part of a core. We assess postural control by S-PASS. A minimally detectable change of 2.22 points on S-PASS could be a good result [72]. It is important to consider measures of activity and functional outcomes when determining whether an intervention is effective. For this reason, we chose the Barthel Index and EQ-5D-5L. There is little evidence that core stabilisation improves ADL [73]. A minimally clinically important difference on Barthel Index is ≈2 points [74]. As for EQ-5D-5L, values of 0.10 on the EQ-Index and 8.61–10.82 on the EQ-VAS are likely to have a clinically important change [75]. Assessing participation outcomes such as quality of life is necessary, according to Gamble et al. [76]. 

A decrease in gait velocity and double support time could represent an attempt at increasing postural stability to reduce fall risk [69]. Specifically, decreased velocity may reduce the body’s momentum, increasing the likelihood of recovering from a loss of balance. A walking speed of 0.8 m/s is predictive of weak functional abilities, while a speed of 0.6 m/s establishes a threshold below which the risk of falling is critical [77]—the minimally clinically important difference in stroke patients (0.6; 0.8 m/s) [78]. 

One of the first objectives of rehabilitation in the subacute phase of the stroke is to achieve optimal trunk control and dynamic balance while sitting. The proposal of this study is to achieve this by training the core muscles. This results in a better balance in sitting, standing, and in a more efficient gait [79]. The earlier these patients can be autonomous, the less time they will be inactive [80], and in this way the adverse effects of immobilisation can be reduced [81]. Additional trunk rehabilitation is beneficial in improving gait performance in sub-acute stroke [82]. Therefore, if the results of this study are positive, we recommend to incorporate these exercises as early as possible in a stroke rehabilitation program. 

Another important goal of this study is to discover whether the treatment effects are sustainable over time, or if the continuous therapeutic input is necessary to maintain the level of function even after the discharge home [83]. In our knowledge, there is no systematic review about the long-term effects of core stability exercises on improving balance and gait in a stroke subacute phase.

## Figures and Tables

**Figure 1 ijerph-18-06615-f001:**
[figure not shown]

[figure not shown]

[figure not shown]
Core stability exercises intervention.

**Figure 2 ijerph-18-06615-f002:**
[figure not shown]
Study scheme.

## Data Availability

Not applicable.

## Abbreviations

ADL	Activities of daily living
BBA	Brunel Balance Assessment
BBS	Berg Balance Scale
CG	Control group
CP	Conventional physiotherapy
CSEs	Core Stability exercises
EG	Experimental group
mRS	Modified Rankin Scale
NIHSS	National Institute of Health Stroke Scale
QoL	Quality of life
RCT	Randomized controlled trial
S-FIST	Spanish version of Function in Sitting Test
S-PASS	Spanish version of Postural Assessment Scale for Stroke
S-TIS 2.0	Spanish version of Trunk Impairment Scale
TENS	Transcutaneous electrical nerve stimulation
